#### **9.4.2 Reporting of Safety Signals**

All safety signals (definition see chapter 9.1.6) must be reported to the Sponsor within 24 hours of the Investigator's first knowledge. Submission is done as for SAE reports (see chapter 9.4.1).

#### **9.4.3 IRB / IECs Safety Reporting by the PI**

The local Institutional Review Board (IRB) and Independent Ethics Committee (IEC) must be informed by the PI or representative of the Sponsor about SAEs, SUSARs, safety signals, the Development Safety Update Report (DSUR) etc. as foreseen by local laws and applicable regulations.

The Sponsor or its representative will notify the Investigator of potential serious risks from clinical trials or any other sources, including the following:

- Suspected, unexpected SAEs.
- Suspected ARs that are both serious and unexpected (SUSAR).
- Any findings from other studies that suggest a significant risk in humans exposed to the IMP.
- Any finding from animal or in vitro testing that suggest a significant risk to humans exposed to the IMP, such as mutagenicity, teratogenicity, or carcinogenicity; or report of significant organ toxicity at or near the expected human exposure.

The DSUR contains information from all clinical trial sites. The Sponsor prepares it, and then submits it to the participating Investigators or Sponsor's representative which submit it to the IRB /IECs.

The Investigator must keep copies of all AE information, including correspondence with the Sponsor or Local Ethics Committees on file.

#### **9.4.4 Regulatory Authorities Safety Reporting by the Sponsor**

Reporting of SAEs, SUSARs, safety signals, the DSUR etc. to the Regulatory Authorities (RA) will be carried out by the Sponsor or its representative in accordance with the local laws and regulations.

The Sponsor's SOPs provide more detail on safety reporting to RAs.

### **9.5 Reporting and Handling of Pregnancies**

Pregnancy per se does not classify as an AE. However, AEs related to a pregnancy have to be reported like any other AEs. Pregnancy should be confirmed by a reliable laboratory test. In the event that a study patient becomes pregnant before visit 3 (grafting of the study product), she will be withdrawn from the study. Patients who become pregnant after visit 3, and thus

have already undergone grafting with the study product, will remain in the study for safety purposes.

All pregnancies occurring during the treatment phase of the study have to be reported to the Sponsor within the same timelines as for SAEs (see chapter 9.4.1) on the Initial Pregnancy Report Form.

The Investigator will contact the study patient at regular intervals by phone during pregnancy and after the estimated date of delivery to enquire about course and outcome of the pregnancy.

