### 4.2 Exclusion Criteria

- Patients tested positive for HBV, HCV, syphilis or HIV
- Patients with known underlying or concomitant medical conditions that may interfere with normal wound healing (e.g. systemic skin and connective tissue diseases, any kind of congenital defect of metabolism including insulin-dependent diabetes mellitus, Cushing syndrome or disease, scurvy, chronic hypothyroidism, congenital or acquired immunosuppressive condition, chronic renal failure, or chronic hepatic dysfunction (Child-Pugh class B or C), severe malnutrition, or other concomitant illness which, in the opinion of the Investigator, has the potential to significantly delay wound healing)
- Severe drug and alcohol abuse
- Pre-existing coagulation disorders as defined by INR outside its normal value, PTT  $> \text{ULN}$  and fibrinogen  $< \text{LLN}$  prior to the current hospital admission and / or at the Investigator's discretion
- Patients with known allergies to amphotericin B, gentamicin, penicillin, streptomycin, or bovine collagen
- Previous enrolment of the patient into the current phase II study
- Participation of the patient in another study with conflicting endpoints within 30 days preceding and during the present study
- Patients expected not to comply with the study protocol (including patients with severe cognitive dysfunction/impairment and severe psychiatric disorders)
- Suspicion of non-accidental injury
- Pregnant or breast feeding females
- Intention to become pregnant during the clinical course of the study (12 months)
- Wounds in the head and neck area as study target area (only applicable for study patients in The Netherlands)
- Enrolment of the Investigator, his/her family members, employees, and other dependent persons

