#### 4.2.1 Contraception Methods

As to ensure appropriate contraception measures and avoid pregnancy in females post menarche, the Investigators are required to instruct the patients on the consistent and correct use of the chosen contraception at each visit during the clinical phase of the study (until visit 10). In addition, the Investigator instructs the patient to call immediately if the selected birth control method is discontinued or if pregnancy is known or suspected.

Highly effective methods of contraception are those that, alone or in combination, result in a failure rate of less than 1% per year when used consistently and correctly and include:

- Established use of oral, inserted, injected or implanted hormonal methods of contraception are allowed provided the patient remains on the same treatment throughout the clinical phase of the study (until visit 10) and has been using that hormonal contraceptive for an adequate period of time to ensure effectiveness.
- Correctly placed copper containing intrauterine device.
- Male condom or female condom used WITH a spermicide (this can be foam, gel, film, cream, suppository).
- Male sterilisation with appropriately confirmed absence of sperm in the post-vasectomy ejaculate.
- Bilateral tubal ligation or bilateral salpingectomy.

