### 7.2.4 Visit 3 - Treatment phase (Grafting, day 0)

The treatment phase of the study is subsequent to the successful manufacturing process of EHSG-KF and comprises the assessment of baseline parameters and the grafting of EHSG-KF or STSG alone onto the wound bed during a surgical intervention.

Following assessments can be done maximally 1 day before grafting or on the day of grafting:

- Checking inclusion and exclusion criteria
- Assessment/reporting of concomitant therapy
- Physical examination
- Routine laboratory (blood count and CrP)

Following assessments have to be done on the day of grafting (day 0):

- Vital signs (heart rate, temperature, blood pressure)
- Wound swabs and clinical evaluation for signs of infection at the study areas
- Photographic documentation of study areas (before and after wound bed preparation, and after application of the control STSG and EHSG-KF)
- Assessment/reporting of adverse events
- Determination and randomisation of study areas (experimental and control areas)

- Facultative biopsies from each wound bed (experimental area and control area) before and after wound bed preparation (e.g. necrectomy, excision) prior to grafting for histological examination of the wound ground.
  - One representative punch biopsy in both wound areas (experimental and control areas) before preparing the wound bed (Biopsies Nr. 2 and 3)
  - Another punch biopsy (experimental and control areas) will be taken after preparing the wound bed (Biopsies Nr. 4 and 5)
- Grafting in the operation theatre
- Plan postoperative visit 4 (6-10 days post grafting)

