#### **7.2.7 Visit 6 - Treatment phase (Third Graft Check, day $28 \pm 3$ )**

- Assessment/reporting of concomitant therapy
- Assessment/reporting of adverse events
- Photographic documentation of study areas
- Vital signs (heart rate, temperature, blood pressure)
- Dressing change
- Assessment/reporting of local infection rate, including wound swabs and clinical evaluation for signs of infection
- Planimetric analysis of the covered (healed) surface area of the experimental area and the control area. Assessment of the ratio of covered surface area to biopsy site or donor site surface area
- Assessment of epithelialisation of study areas and wound closure
- Plan postoperative visit 7 ( $60 \pm 3$  days after grafting)

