#### **7.2.8 Visit 7 - Post-treatment phase (Follow-up, day 60 ± 3)**

- Assessment/reporting of concomitant therapy
- Assessment/reporting of adverse events
- Photographic documentation of study areas
- Vital signs (heart rate, temperature, blood pressure)
- Assessment of epithelialisation of study areas and wound closure
- Plan postoperative visit 8 (90 ± 5 days after grafting)

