#### **7.2.11 Visit 10 - Post-treatment phase (Safety-Follow-up, 1 year ± 30 days)**

- Assessment/reporting of concomitant therapy
- Assessment/reporting of adverse events
- Vital signs (heart rate, temperature, blood pressure)

- Photographic documentation of study areas
- Assessment of scar quality using
  - Cutometer®
  - POSAS-questionnaire
  - DSM ColorMeter®-Measurement
- Surface area measurements (cm^2) for study areas via digital image analysis (to obtain a baseline value to calculate % change with growth)
- Physical examination
- QOL questionnaires
  - EQ-5D and BSHS-B for patients ≥18 years
  - EQ-5DY and PedsQL for patients <18 years
- Health Costs after a Skin Transplantation
- Optional biopsies: one from the experimental area and one from the control area (biopsies Nr. 8 and 9), for routine histology and immuno-histochemistry
- Plan postoperative visit 11 (2 years ± 30 days after grafting)

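### The duty to report a pregnancy to the sponsor stops with the treatment phase (visits 3 to 6), although contraception advice and safety follow-up continue to visit 10 and beyond

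*Protocol*

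**What the plan says.** Section 9.5 opens by saying that a pregnancy does not in itself count as an AE, while AEs related to a pregnancy are reported in the usual way. A patient who becomes pregnant before grafting is withdrawn. One who becomes pregnant after grafting stays in for safety reasons, with no upper visit limit. The reporting rule follows: "All pregnancies occurring during the treatment phase of the study have to be reported to the Sponsor", within SAE timelines and on the Initial Pregnancy Report Form. The investigator then follows the course and outcome by phone.

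Section 4.2.1 uses a longer window. At each visit until visit 10, investigators must instruct female patients past menarche on contraception, and the patient is told to "call immediately if the selected birth control method is discontinued or if pregnancy is known or suspected". Section 4.2 excludes women who intend to become pregnant during the 12-month clinical course.

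On the phase itself, section 7.2.4 says "The treatment phase of the study is subsequent to the successful manufacturing process of EHSG-KF". Table 6 and the headings of sections 7.2.4 to 7.2.7 assign visits 3 to 6 to it.

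**The concern.** The reporting window in section 9.5 is tied to a phase that ends about four weeks after grafting, while the protocol's other pregnancy provisions run for a year or have no end. Followed literally, the rule lets a site learn of a pregnancy at month 4, keep the patient in the study for safety, phone her through delivery, and send the sponsor nothing unless an AE or SAE occurs.

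Some sites will report such a pregnancy anyway and others will not, so the sponsor's record of pregnancies after exposure to an investigational cell-based product could be incomplete and uneven. The stakes are limited to safety reporting. Randomisation, the primary endpoint, the significance level and power are not involved.

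**Working it through.** **Which visits belong to the treatment phase**

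| Source | Content |
|---|---|
| Table 6 | Treatment phase: visits 3 to 6. Post-treatment phase: visits 7 to 10. Long-term follow-up: visits 11 and 12 |
| 7.2.7, heading begins | "Visit 6 - Treatment phase (Third Graft Check" (day 28 ± 3) |
| 7.2.8, heading begins | "Visit 7 - Post-treatment phase (Follow-up, day 60 ± 3" |
| 7.2.11, heading begins | "Visit 10 - Post-treatment phase (Safety-Follow-up, 1 year ± 30 days" |
| 10.3.8 | AEs are listed by three phases: pre-treatment, treatment, post-treatment |
| 4.2.1 | The first year has a different name, the clinical phase, which ends at visit 10 |

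The treatment phase is therefore a fixed term covering visits 3 to 6. The protocol gives no calendar day on which it closes, so both possible ends are used below: visit 6 itself, or the start of the post-treatment phase at visit 7.

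**Whether another route catches the pregnancy**

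- Sections 9.2, 9.4.1, 9.4.2 and 9.6 cover AEs, SAEs and safety signals. An uneventful pregnancy is none of these.
- The patient's call (4.2.1) goes to the investigator, and the phone follow-up (9.5) runs from investigator to patient. Neither reaches the sponsor.
- Table 5 schedules a pregnancy test at visit 1 only.

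No other section of the protocol supplies the duty.

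**Length of the uncovered period, from the end of the treatment phase to visit 10**

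Inputs (Table 6): visit 6 = 28 ± 3, so day 25 to 31; visit 7 = 60 ± 3, so day 57 to 63; visit 10 = 1 year ± 30 days, so day 335 to 395.

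Formula: gap = day of visit 10 − day the phase ends; nominal share = nominal gap / 365.

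| Phase ends at | Nominal gap | Shortest | Longest | Nominal share |
|---|---|---|---|---|
| Visit 6 | 365 − 28 = 337 days | 335 − 31 = 304 | 395 − 25 = 370 | 337/365 = 92% |
| Visit 7 | 365 − 60 = 305 days | 335 − 63 = 272 | 395 − 57 = 338 | 305/365 = 84% |

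Long-term follow-up to visit 12 adds a nominal 1095 − 365 = 730 days that are also outside the duty.

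**How many pregnancies might be involved**

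The protocol does not give the number of women. Assume, as the extreme for the number at risk, that all 15 patients could become pregnant. Section 4.2.1 puts the failure rate of highly effective methods below 1% per year when they are used consistently and correctly. Under that rate the expected number over the gap is below 15 × 0.01 × 337/365 = 0.14, or 15 × 0.01 × 305/365 = 0.13. With 12 patients the figures are 0.11 and 0.10. These values depend on perfect use. Inconsistent or abandoned contraception would raise them, and the protocol gives no rate for that.

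**The case against.** The strongest reply is that the windows merely differ and do not contradict each other. Nothing says the pregnancy-report window must equal the contraception or AE window. The protocol names no fetal hazard from a single autologous graft, and section 9.7 describes its living components as non-immunogenic. Most of what matters for safety is already covered: pregnancy-related AEs are reported to visit 12, a congenital anomaly is an SAE due within 24 hours, and the phone follow-up is not limited to any phase. What is missing is one initial form for an uneventful pregnancy.

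That is a fair account of the size of the gap, and it is why this is a minor point. It does not remove the gap, because the follow-up of an uneventful pregnancy stays between site and patient.

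Three narrower objections also have substance:

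- Section 4.2.1 obliges investigators to instruct on contraception and does not make its use a condition of entry. The comparison here is therefore with the period of instruction.
- Phase labels are not fully uniform. Visits 11 and 12 are post-treatment in their headings but long-term follow-up in Table 6. The phrase in section 9.5 may simply be a slip for the clinical phase. That would call for the same correction, and none of these labels places visits 7 to 10 in the treatment phase.
- The Initial Pregnancy Report Form is not available and might state its own window. The conclusion is about the protocol text only.

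**Conclusion.** The point holds as a minor safety-reporting correction. As the protocol is written, an uncomplicated pregnancy arising in the post-treatment phase carries no stated duty of report to the sponsor. This applies to 84% to 92% of the nominal year in which contraception is instructed after grafting, depending on whether the treatment phase is taken to end at visit 7 or visit 6. The conclusion rests on reading the phase as Table 6 and the visit headings define it. Complicated pregnancies and congenital anomalies remain reportable. The expected number of cases is well below one under correct contraceptive use; no firm bound can be given otherwise.

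**What to change.** In section 9.5, replace the reference to the treatment phase with: from grafting (visit 3) until at least visit 10. If the sponsor prefers the window to match AE collection, extend it to visit 12. Leave the SAE timelines, the report form and the phone follow-up unchanged, and check that the form's own instructions give the same window. The cost is one phrase at the next amendment and at most a few extra forms. No analysis changes.

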## 9.6 Follow-up of (Serious) Adverse Events

If a non-serious AE is ongoing at the date of the patient's last visit, it will be followed up to resolution at the discretion of the Investigator.

If a SAE is ongoing at the date of the patient's last visit, it has to be followed up until resolution or its stabilisation. The follow-up will be recorded in the eCRF.

Follow-up investigations may also be necessary according to the Investigator's medical judgment even if the study patient has no ongoing AE at the end of the study.

All information has to be documented in the source documents.

In case of a study patient lost to follow-up, efforts should be made and documented to contact the patient to encourage him/her to continue study participation as scheduled. In case of mild (Grade 1) AEs (according to the Investigator's discretion) a telephone call to the patient may be acceptable.

## 9.7 Anticipated Adverse Events

All complications that may be encountered during this study are AEs although they are, in all anticipated likelihood, not a direct consequence of the study product.

Rather, these complications or symptoms are well-known classical findings associated with any type of grafting of skin defects, namely infection, bleeding, unintended mechanical trauma (sheering forces acting upon fresh grafts) that may all lead to partial or complete graft loss. The management of these AEs encompasses additional dressing changes with wound cleansing/wound debridement (including vacuum-system-application), systemic and/or topical antibiotic therapy, and eventually re-grafting operations according to type and severity of the respective complication. In general, these complications are manageable in a straightforward way.

It is more difficult to envision AEs that are truly and solely arising from the use of EHSG-KF given the fact that all viable components are autologous and thus non-immunogenic, and all non-viable components (basically representing extracellular matrix components) have already been used in other clinical contexts without showing any significant AEs.

## 10. Statistical Analyses

### Hypothesis:

The experimental treatment results in a better ratio of closed (healed) wound surface area to biopsy site surface area than the ratio of closed (healed) wound surface area to donor site surface area with the standard treatment. Apart from evaluating efficacy and safety of the intervention, this study is also intended to generate hypotheses for upcoming phase III studies.

### 10.1 Analysis Plan

#### 10.1.1 Final analysis

The final analysis will be conducted once all patients have completed the month 12 end of study visit (V10).

#### 10.1.2 Long-term follow-up analysis

The long-term follow-up analysis will be conducted once all patients have completed the 2 follow-up visits, 2 and 3 years after denovoSkin™ application, V11 and V12 respectively.

#### 10.1.3 Interim analysis

In the interest of the development of the product, the Sponsor might extract data by means of an interim analysis from the first 12 patients who received denovoSkin™ to perform a submission to a regulatory agency for a request of designation such as for example the priority Medicines scheme (PRIME) in Europe and the Regenerative Medicine Advanced Therapy (RMAT) in the US. This will not interfere with the conduct of the study for the following up to 3 patients. The interim analysis will be done on a database that has been cleaned up to that the month 3 visit (V6) and will be performed on part of the efficacy and safety endpoints. The interim analysis will include the statistical analysis on the primary efficacy endpoint (final results will not change) and only descriptive statistics on the other endpoints, described in an interim-specific SAP (statistical analysis plan). A correction for multiple comparisons is considered not needed.

### 10.2 Determination of Sample Size

The primary endpoint (i.e. the ratio of covered surface area to biopsy site / donor site surface area at 4 weeks post grafting) will be analysed after a logarithmic transformation and the treatment effect estimate will be expressed as a percentage of additional coverage obtained with EHSG-KF comparatively to STSG.

Published data of cultured skin substitutes in a series of 10 patients (Boyce 1995, Table 11) show on the logarithm of the ratio of covered surface area to biopsy site surface area (also named expansion ratio) at 1 month post grafting a standard deviation of 0.97 with a mean of 1.98 (corresponding to a geometric mean of 7.24 on the original scale). Data from the EHSG-KF Phase I clinical trial (excluding one patient with 100% graft loss attributable to patient noncompliance and manipulation of the dressing post-operatively) show on the logarithm of the ratio of covered surface area to biopsy site surface area at 3 weeks post grafting a standard deviation of 0.99 with a mean of 1.80 (corresponding to a geometric mean of 6.05 on the original scale). A standard deviation of 1.00 will be assumed for the difference (on the logarithmic scale) between the two treatments, corresponding, for instance, to a common standard deviation of 1.00 on each treatment site with a correlation between sites of 0.50.

The ratio of covered surface area to biopsy site / donor site surface area at 4 weeks post grafting is expected to be at least 145% higher on EHSG-KF than on STSG (corresponding, for instance, to ratios of 7.35 and 3.00, respectively).

- Assuming a standard deviation of 1.00 for the paired difference between the 2 log(ratios), a sample size of 12 evaluable patients would be required in order to achieve a power of 80% to detect a treatment effect corresponding to an increase of 145% with EHSG-KF (i.e. to a difference of 0.90 on a logarithmic scale) when using a one-sample t-test at two-sided significance level of 5%.  
A claim of study success will be made when the two-sided test passes the significance level of 0.05.
- All secondary endpoints will be tested in a strictly exploratory fashion only.

**Table 11:** Criteria for sample size determination

| Criteria                                                                                   | Value |
|--------------------------------------------------------------------------------------------|-------|
| Standard deviation of the paired difference between log(ratio) EHSG-KF and log(ratio) STSG | 1.00  |
| Difference in log-ratio to detect (effect size)                                            | 0.90  |
| Statistical power                                                                          | 0.80  |
| P-value (two-sided)                                                                        | 0.05  |

## 10.3 Planned Analyses

### 10.3.1 Analysis Populations

Since randomization takes place during the operation procedure (or shortly before, as described in chapter 3.5), it is assumed that there is no difference between "randomized" and "treated" patients. Therefore, the following analysis populations are defined.

mITT (modified ITT) population: consists of all randomized/treated patients having at least 1 post-surgical measurement. The mITT population will be used for the analysis of efficacy variables, and statistical analysis will be done "as randomized".

PP (per protocol) population: consists of all patients adhering to the protocol. The PP population is subset of the mITT population. Subjects with major protocol deviations that might impact the primary endpoint will be excluded from this population. These deviations will be

determined before database lock. The PP population will be used for the analysis of efficacy variables, and statistical analysis will be done “as randomized”.

SAF (safety) population: includes all patients who have received a surgical treatment, irrespective of satisfying other criteria. This population will be used for the analysis of safety and tolerability, and statistical analysis will be done “as treated”.

The primary analysis will be performed using the mITT as primary analysis population, and PP as supportive. Secondary and exploratory efficacy analyses will only use the mITT. Safety analyses will be presented using the SAF.

Implications of administration of OOS products (see chapter 3.2.8) on analyses are expected to be minimal considering that only OOS products with a positive risk/benefit ratio on patient safety will be administered. Data of patients with OOS products administered are included in the analyses.

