#### **4.3.3 Replacement of Patients**

The following points describe the procedure of replacement/enrolment of patients:

- Drop-out prior to grafting: Patient is replaced
- Drop-out after grafting: Patient is not replaced

Patients will continue to be enrolled in the study until 12 patients were evaluated for primary endpoint (visit 6) (see chapter 10.2).

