#### **4.4 Data Collection and Follow-Up for Withdrawn Patients**

In the case of premature withdrawal from the study, either due to patient preference or Investigator-led withdrawal, where possible, the reason(s) will have to be recorded on the "Premature Study End" form. This form needs to be completed for each prematurely discontinued patient.

Patients who discontinue the study prematurely will take part in a safety examination including a physical examination, vital signs, and routine laboratory tests, if possible. The data should be recorded in the eCRF in the "Premature Study End" form. Patients withdrawing after visit 10 due to 100% graft loss (before visit 10) do not need to perform the safety examination.

The PI needs to ensure appropriate, further medical care for the patient outside of the study. Ongoing AEs should be followed to resolution at the discretion of the Investigator. These follow-ups will not be recorded in the eCRF. Ongoing SAEs have to be followed up until recovery or stabilisation and need to be documented in the eCRF and reported according to chapter 9.

Data collected up to the time point of the withdrawal of the patient and data from the safety examination (if possible) will still be collected in the eCRF and analysed.

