### 8.2.8 Number and Type of Adverse Events

Adverse events will be evaluated and counted as secondary endpoints.

Adverse events occurring from visit 2 (Biopsy) until visit 12 (3 years post-grafting) will be included.

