## 9. Safety

All adverse events (AEs) and all serious adverse events (SAEs) occurring from visit 2 (Biopsy) until visit 12 (3 years post-grafting) will be collected. They will be fully investigated and documented in source documents and eCRF.

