### **10.3.8 Secondary Analyses – AE Reporting (during full study duration)**

All adverse events will be listed by patient, phase (pre-treatment, treatment, post-treatment) and date of onset.

Adverse events with an onset date during the treatment phase will be summarized in a frequency table. Adverse events with an onset date during the pre-treatment phase or the post-treatment phase will be summarized the same way.

If appropriate, additional tables will be prepared for selected adverse events (e.g.: adverse event leading to treatment discontinuation, serious adverse events).

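### The safety set begins at grafting while adverse events count from the biopsy, so the planned pre-treatment adverse event table covers only patients who reached grafting

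*Protocol*

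**What the plan says.** Protocol section 10.3.1 defines one safety set: "SAF (safety) population: includes all patients who have received a surgical treatment, irrespective of satisfying other criteria". It is analysed as treated, and the section adds: "Safety analyses will be presented using the SAF". No other set is named for safety. The same section explains that randomisation happens at or shortly before the operation, so that "it is assumed that there is no difference between 'randomized' and 'treated' patients".

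Other sections start the safety record earlier:

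- Section 9: "All adverse events (AEs) and all serious adverse events (SAEs) occurring from visit 2 (Biopsy) until visit 12 (3 years post-grafting) will be collected".
- Section 8.2.8, on AEs as secondary endpoints: "Adverse events occurring from visit 2 (Biopsy) until visit 12 (3 years post-grafting) will be included".
- Section 9.3.1 names AEs during biopsy harvesting among the events to be assessed for relatedness.
- Section 10.3.8 promises a listing of every AE by patient, phase and onset date, then a frequency table for the treatment phase, and then: "Adverse events with an onset date during the pre-treatment phase or the post-treatment phase will be summarized the same way".
- Section 4.4, on withdrawn patients: data up to withdrawal and "data from the safety examination (if possible) will still be collected in the eCRF and analysed".
- Section 4.3.3: "Drop-out prior to grafting: Patient is replaced".

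**The concern.** Between visit 2 (biopsy) and visit 3 (grafting) lies the manufacturing period, given as an average of 32 days (SD 4, range 26 to 38) in section 1.3.1. Section 4.3.2 lists reasons for withdrawal in that interval: unresolved infection at a study site, deterioration leading to palliative care, too few viable cells, a graft that is not released, or a wound that no longer needs grafting. Several of these are health outcomes or follow directly from them.

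If safety summaries rest on grafted patients, membership of the pre-treatment table depends on what happened during the very period it describes. The table would then look like an account of safety from biopsy to grafting while leaving out the patients who did worst in that interval. The number who were biopsied and never grafted would not appear as a denominator anywhere.

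**Working it through.** **1. Which operation the safety set refers to.** The term is not defined. Three features of the text point to grafting:

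- Section 10.3.1 equates treated with randomised, and randomisation takes place at grafting (section 3.5).
- The set is analysed as treated, which has no meaning for a patient who has no allocation.
- Tables 5 and 6 and section 7.2.3 place the biopsy in the pre-treatment phase, and section 7.2.4 starts the treatment phase only after manufacturing has succeeded.

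**2. One patient followed through the rules.** Take a patient biopsied at visit 2 and withdrawn before visit 3.

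| Rule | Result for this patient |
|---|---|
| Sections 6.3, 8.2.8 and 9 | AEs are collected and count as a secondary endpoint |
| Section 9.3.1 | Biopsy AEs are assessed for relatedness |
| Section 4.4 | Data are collected and analysed |
| Section 10.3.8, listing | Events appear, if the listing is not limited to the safety set |
| Section 10.3.8, pre-treatment frequency table | Not counted, because section 10.3.1 applies |
| Section 4.3.3 | Replaced by another patient |

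The pre-treatment frequency table therefore disagrees with the endpoint definition and with section 4.4.

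**3. What the table can show.** Every member of the set was alive and eligible at grafting. The count of deaths between biopsy and grafting in that table is 0, whatever the true number. The same holds for a switch to palliative care before grafting, which is itself a withdrawal criterion. This step needs no assumption beyond the reading in step 1.

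**4. How many patients.** The plan's own figures come first. Section 10.2 uses a one-sample t-test at two-sided 5%, a difference of 0.90 and an SD of 1.00. With 12 patients the noncentrality is 0.90 × √12 = 3.118 and the exact power is 81.0%; with 11 it is 76.7%. So 12 reproduces. The synopsis allows up to 15 randomised patients, and 12/15 = 0.80 corresponds to 20% loss. That allowance starts at randomisation, so it does not cover losses between biopsy and grafting.

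The protocol gives no rate for those earlier losses. Let g be the number grafted and p the assumed share of biopsied patients never grafted. Then biopsied = g/(1 − p) and left out = g × p/(1 − p).

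| Assumed p | Left out, g = 12 | Left out, g = 15 |
|---|---|---|
| 10% | 12 × 0.1/0.9 = 1.3 | 15 × 0.1/0.9 = 1.7 |
| 20% | 12 × 0.2/0.8 = 3.0 | 15 × 0.2/0.8 = 3.8 |
| 30% | 12 × 0.3/0.7 = 5.1 | 15 × 0.3/0.7 = 6.4 |

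The share left out is p by definition, so the table only turns an assumed rate into patients. It does not estimate the rate.

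**The case against.** **The term could include the biopsy.** Section 5.3 lists biopsy Nr. 1 as invasive, Appendix 1 places it in an operating or procedure room, and the safety set, unlike the mITT, is not worded in terms of randomisation. Literally, a biopsied patient might qualify. This stands as far as it shows an ambiguous term. It does not rescue the rule: if biopsied patients are in the only safety set, the treatment and post-treatment tables would count patients who never received a graft. One set cannot serve all phases.

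**The events are not lost.** A reader might infer that these events disappear from safety reporting. The documents do not support that. Section 10.3.8 promises a listing of all AEs, section 9.4.1 requires serious AEs to be reported within 24 hours, and section 11.5 gives the safety board a safety evaluation. With so few patients a listing is informative. This objection stands and confines the point to summary tables and their denominators. A listing still gives no denominator and does not correct a table selected on outcome.

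**Harm from the biopsy or the wait is not shown.** A reader might also infer that harm specific to EHSG-KF is being understated, because only EHSG-KF needs the biopsy and the delay. The text is against this. Section 7.3.2 allows the biopsy to be cut from skin harvested for another site or from a biopsy for cultured epithelium. Section 12.8 describes such biopsies as part of standard care in severe burns with limited donor sites and calls the added risk negligible. Section 1.3.2 asks the surgeon to justify why wounds could not have been covered by standard care, so that none is kept open for the trial. The control is within the patient, so a death before grafting has no comparator. This objection stands in full.

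**A treated-patient safety set is common, and the SAP may add sets.** True, but here the protocol itself fixes the set for all safety analyses while promising a pre-treatment table and an endpoint that starts at biopsy.

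**Conclusion.** The point holds as an internal inconsistency in how safety is summarised. On the natural reading of section 10.3.1, the pre-treatment AE table is restricted to patients who survived and stayed eligible until grafting, and those withdrawn and replaced earlier are in no summary denominator. This conflicts with sections 4.4, 6.3, 8.2.8 and 9.

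The firm part of its size is that the table must show zero deaths between biopsy and grafting. The number of patients concerned is unknown; the figures of about 1.3 to 6.4 rest wholly on assumed loss rates of 10% to 30% and should not be quoted as an estimate of the trial's losses.

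What is at stake is an incomplete description of the course before grafting, not a demonstrated bias in the safety of EHSG-KF. Sample size, power, the primary analysis and the success claim are untouched. Severity is moderate.

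**What to change.** In section 10.3.1, and in the SAP to match:

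- Define the term for surgery in the existing safety set as the grafting operation.
- Add a second safety set: all patients in whom biopsy Nr. 1 was taken, except patients biopsied under deferred consent who then decline, because section 12.8 bars the use of their data.
- Use the new set for the AE listing, the pre-treatment AE table and deaths from visit 2.
- Keep the grafted set as denominator for the treatment and post-treatment tables.
- State both denominators, and report how many patients were biopsied but not grafted, with reasons.

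The cost is a few sentences, one more analysis set and one more denominator. AEs are already collected from visit 2, so no new assessment is needed. One limit should be stated with the results: under section 4.4 the safety examination after withdrawal takes place only if possible, and later follow-up of ongoing non-serious AEs is not entered in the eCRF, so the record for these patients largely ends at withdrawal.
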